## Abstract

**Background:**

Primary progressive aphasia is a language-led dementia, often associated with frontotemporal dementia. It presents as insidious deterioration of language skills (e.g. naming objects and understanding complex sentences), with relative sparing of cognitive skills initially. There is little research examining the effectiveness of communication skills training for primary progressive aphasia, yet speech and language therapists (SLTs) report regularly using this in clinical practice. ‘Better Conversations with Primary Progressive Aphasia’ has potential to reduce barriers and increase facilitators to conversation and consequently improve confidence in communication and quality of life for people living with primary progressive aphasia and their conversation partners. The aim of this pilot study is to examine the feasibility of running a trial of the ‘Better Conversations with Primary Progressive Aphasia’ intervention.

**Methods:**

A single blind, randomised controlled pilot study will recruit 42 participants with primary progressive aphasia and their conversation partners across seven UK National Health Service Trusts. Participants will be randomised on a 1:1 basis, stratified by site, to receive either the ‘Better Conversations with Primary Progressive Aphasia’ intervention (21 couples) or no speech and language therapy treatment (21 couples). Participants are recruited by SLTs who will conduct pre-intervention assessment (week 1) and deliver the intervention (weeks 2 to 5). Junior researchers, who are blinded to allocation, will complete post-intervention measures (week 6). SLTs complete 9 h of training to prepare them to deliver the intervention. The primary objective of the study is to establish for a phase III effectiveness study whether the program can be delivered as intended in a UK National Health Service setting. Specifically, it will establish (1) the acceptability of randomisation, (2) an assessment of treatment fidelity to determine necessary levels of SLT training, (3) the most appropriate primary outcome measure, (4) sample size requirements, (5) predicted patient recruitment and retention rates and (6) refined inclusion criteria.

**Discussion:**

Insights from this study will be of relevance to guide development of future research and in particular, trials of therapeutic interventions in PPA, as well as for clinical care for this population.

**Trial registration:**

Retrospectively registered 28/02/2018 ISRCTN10148247

**Electronic supplementary material:**

The online version of this article (10.1186/s40814-018-0349-6) contains supplementary material, which is available to authorized users.

## Background

The prevalence of dementia is increasing, and it is anticipated that by the year 2050, there will be more than 131.5 million living with the diagnosis worldwide [1]. Primary progressive aphasia (PPA) describes a group of language-led dementias, often associated with frontotemporal dementia and considered the leading cause of dementia in people of working age [2, 3]. PPA initially presents solely as a language difficulty with impairments that superficially resemble classical stroke aphasia syndromes but worsening over time. There are three major PPA syndromes, namely semantic variant that affects the use and understanding of word meanings, logopenic variant that results in difficulties in word retrieval, and non-fluent agrammatic variant where individuals may present with either or both verbal dyspraxia and grammatical errors [3]. In many cases, other cognitive deficits (e.g. with memory) may not present for several years. As a result, people with PPA are often highly motivated to seek speech and language therapy. Perhaps, as a result of this retained awareness, people with PPA are prone to low self-esteem and poor confidence [4].

The research evidence for speech and language therapy interventions for PPA is sparse and is predominantly limited to naming therapies, word finding difficulty being a common impairment [5–11]. However, naming is often not the main limitation on communication function in PPA, and interventions are required to address real world communication function. This is particularly relevant given that prognosis in PPA is for loss of function, rather than improvement as in stroke aphasia, and there is a need to engage family/carers in speech and language therapy. Yet, there is a paucity of literature examining the impact that speech and language therapists (SLTs) can have in supporting a person with PPA and their family/carers with conversation [12, 13]. Nevertheless, SLTs in clinical practice report using communication training programs more often than naming therapies [14]. This is not surprising when reports suggest many patients disengage from naming therapies due to the frustration of practising individual words they will inevitably lose as the disease progresses [2].

SLTs have been reported to prioritise working on communication between people with PPA and their conversation partners (CPs), specifically targeting the use of meaningful strategies for both the person and their family members [15] using a variety of communication training approaches from the stroke and brain injury literature that have not been trialled for PPA [16]. Communication skills training has a growing evidence base in these fields [17, 18]. Programs have in common individualised feedback (often video-based) on facilitators (behaviours that help conversation such as using multi-modal communication—speaking, gesture, drawing and other communication aids) and barriers (behaviours that create problems in conversation such as the use of ‘test’ questions, asked by the CP despite already knowing the answer) to communication, followed by strategy training, with the aim of maximising the success of everyday conversations [19]. Whilst many such programs focus on training the CP only, Better Conversations with Aphasia (BCA) [20] aims to change the conversation skills of both a person with post-stroke aphasia and a CP [21–23]. BCA is a free online package consisting of a therapy manual and training materials for SLTs. Since its launch in 2013, it has attracted over 5000 users worldwide. BCA utilises video feedback to enable participants to reflect on communication facilitators and barriers, and the authors believe this to be a key mediator for improved conversation skill. In a UK-wide survey, a high proportion of SLTs report working with both the person with PPA and their CP and using BCA as a tool to support this therapy above other tools that only target the CP [16], thus motivating BCA as a target for adaptation to PPA over other possible alternative stroke aphasia programs.

In summary, the evidence base for communication training in PPA is limited, yet front-line SLTs favour this over naming programs with a stronger evidence base. This is because SLTs identify the need to support both a person with PPA and their CPs, who are equally distressed about conversation breakdown. We presently lack evidence to guide effective communication-based interventions in PPA. In response to this gap in the evidence base, the authors undertook a research study to develop and pilot a communication skills training program for people with PPA and their CPs. The BCA program for post-stroke aphasia was initially adapted to meet the needs of people with PPA using data collected from a UK-wide survey of speech and language therapy practice [16] and a systematic review of the research literature on functional communication focused interventions for people with PPA and their families [24]. It was further refined with SLTs who participated in a process using a nominal group consensus technique [25] to agree with the intervention objectives and with people with PPA and their families who took part in a series of focus groups. A BCPPA steering group (of people with PPA, their family members and expert professionals) was established at the start of the work to provide advice and feedback on all aspects of study management, including the co-production of materials for the program and support for future dissemination of results. In terms of the MRC guidance on development and evaluation of complex interventions [26], intervention refinement constituted phase I work to fully define BCPPA. This paper summarises the phase II randomised controlled pilot study protocol for the BCPPA program. Our UK-wide survey of SLTs [16] shows that there is no standard speech and language treatment for people with PPA, thus it is not possible to have a usual care group for the study. Instead, a no speech and language therapy treatment control group has been used. The protocol has followed the CONSORT (Consolidated Standards of Reporting Trials) guidelines and the SPIRIT (Standard Protocol Items: Recommendations for Interventional Trials) statement [27] as well as the TIDieR (Template for Intervention Description and Replication) checklist and guide [28].

### Aim

The primary aim of this study is to pilot the BCPPA program compared to a no speech and language therapy treatment control group over participating sites to establish for a main trial whether BCPPA can be delivered as intended in an NHS setting. Specifically, the aim of piloting the BCPPA program compared to a no speech and language therapy treatment control group is to establish:The acceptability of randomisationAn assessment of BCPPA treatment fidelity to determine necessary levels of SLT trainingThe most appropriate primary outcome measureSample size calculationPredicted patient recruitment and retention ratesRefined inclusion criteria

## Methods

### Design

This is a single blind, randomised controlled pilot study with BCPPA treatment versus no speech and language therapy treatment. Participants will be involved for a total of 6 weeks: pre-intervention measures (week 1); intervention/control (weeks 2–5); and post-intervention measures (week 6). See Fig. 1 for participant flow chart through study.

**Fig. 1 Fig1:**
[figure not shown]
BCPPA participant flowchart through study

### Setting

The seven participating NHS sites are located in England. Local collaborators (SLTs) at these sites will recruit participants, obtain consent, complete pre-intervention measures and deliver the BCPPA intervention across outpatient and community settings over a 20-month period.

### Population

The study includes adults (> 18 years) with a diagnosis or potential diagnosis of PPA (in view of the difficult and often protracted diagnostic process). See Table 1 for inclusion and exclusion criteria.

**Table 1 Tab1:** Inclusion and exclusion criteria for potential participants

Inclusion criteria	Local collaborators at participating NHS sites will judge potential participants against the following criteria: (a) Have a diagnosis or possible diagnosis of PPA (b) Have some ability to communicate and understand communication in order to participate in the BCPPA program; (c) Are able to see and hear well enough to participate in the BCPPA program (d) Are functionally able to engage in the BCPPA program (i.e. able to maintain some concentration and remain in a 60–90 min session, minimal challenging behaviour that would be unlikely to cause disruption) (e) English as their language of daily use; (f) Have a conversation partner (CP) who is able to and consents to participating in the project.
Exclusion criteria	People will be excluded from participation in the pilot if they: (a) Have a history of brain lesions or major head trauma; (b) Have major physical illness or disability which could impact on participation; (c) Present with a major psychiatric diagnosis; (d) Present with prominent behavioural disturbance; (e) Present with prominent episodic memory, visual memory, or visuoperceptual impairments.

Note: The researchers acknowledge that the inclusion criteria may result in significant heterogeneity across participants—please refer to discussion of limitations

### Identification and recruitment of participants

Local collaborators will be asked to identify people referred to their service who are suitable for the pilot using the inclusion and exclusion criteria (Table 1) and invite them to participate. Local collaborators will complete a log to record the number of people with a diagnosis of PPA who do not meet the inclusion criteria, they will also record the number of people who are eligible but who have declined to participate in the study and their reasons why if provided. People who meet the inclusion criteria will not be under any obligation to take part in this research and this will be made clear from the outset. Potential participants will be provided with a participant information sheet (see Additional file 1) before informed consent is obtained at least 48 h later (see Fig. 2 for consent flowchart).

**Fig. 2 Fig2:**
[figure not shown]
Consent flowchart

All participants in the study will be in the mild to moderate stages of PPA and therefore would generally be expected to be competent to give informed consent to participate, provided that appropriate care is taken to explain the research and sufficient time is allowed for them to reach a decision. Due to the brief nature of the participants’ involvement in the study (5 weeks) it is not anticipated that decision-making capacity will change over this time; however, this will be monitored by the local collaborator who obtains consent following the Mental Capacity Act (MCA) [29], Royal College of Speech and Language Therapists (RCSLT) guidelines [30] and Good Clinical Practice Standards [31]. The local collaborators are specialist SLTs with considerable experience of supporting individuals with communication and cognitive impairment and who complete annual mandatory training on the MCA [29] and issues related to obtaining consent. If a local collaborator has any doubts regarding the capacity of a person with PPA to provide informed consent for this study, advice will be sought from the first author or an appropriate professional involved in their care, e.g. the GP, as is standard practice. Participant information sheets and consent forms (see the Additional files) have been designed to be dementia friendly [32] and modified with advice from the study’s steering group of people with PPA and their carers (Additional file 2).

### Randomisation

Randomisation will be conducted by the final author using a random number generator and stratified by site using blocks of four to balance across BCPPA treatment and no speech and language therapy treatment groups within each site. Block sizes will not be disclosed to local collaborators. Local collaborators will be informed of participant group allocation via email after pre-assessment has been completed.

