Study limitations include the inability to blind participants to group allocation, a common barrier in behavioural studies. Those allocated to the control group will not receive any intervention for 4 weeks as there is no comparable standard care intervention. Similarly, it is not possible to blind local collaborators delivering the intervention. For this reason, post-intervention assessment is not completed by the local collaborators but by pairs of junior researchers who will be blinded to group allocation. The inclusion criteria for this study may result in significant heterogeneity across participants in terms of language profile and communication difficulties, making it difficult to compare participants’ skills pre and post intervention. Thus, a range of outcome measures are being piloted across language, communication, and quality of life to identify the most sensitive across all participants. BCPPA is designed to be tailored to an individual’s needs, which may result in variation in the types of strategies identified and practiced. To counter this, the key components of BCPPA remain fixed, and measures of fidelity will demonstrate the consistency with which the intervention in delivered. A further potential limitation is ascertainment bias since access to speech and language therapy for PPA varies widely across the UK, and some of the likely barriers to access (socio-economic, cultural, linguistic, etc.) could also influence BCPPA outcomes. Despite these limitations, this study represents an important step toward a future full-scale RCT to determine the effectiveness of BCPPA for people with PPA and their family members.

The results of this study will be disseminated via presentations at national and international conferences and submitted for publication in peer reviewed scientific journals. In the medium term, the BCPPA program and training materials will be made available to SLTs via UCL’s public e-learning platform, alongside BCA [18]. With support from the study steering committee, results will be disseminated through professional and user group networks via publications and presentations, for example, at the PPA support group branch of the Rare Dementias Support Group based at UCL (http://www.raredementiasupport.org/).

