### Trial status

Trial registration number ISRCTN10148247. Recruitment commenced in November 2017 and is due to end in March 2019.

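### The article prints the fixed block size of four per site while recruitment is open, which weakens its own rule of withholding that size from the recruiting therapists

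*Protocol article*

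**What the plan says.** The Methods part of the abstract sets the ratio: "Participants will be randomised on a 1:1 basis, stratified by site". The Randomisation section adds that the list is "stratified by site using blocks of four to balance across BCPPA treatment and no speech and language therapy treatment groups within each site", and follows this directly with "Block sizes will not be disclosed to local collaborators". The same section says when therapists learn the arm: "Local collaborators will be informed of participant group allocation via email after pre-assessment has been completed".

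The Setting section gives these therapists several roles: "Local collaborators (SLTs) at these sites will recruit participants, obtain consent, complete pre-intervention measures and deliver the BCPPA intervention". The section on identification and recruitment also leaves the choice of candidates to them: "Local collaborators will be asked to identify people referred to their service who are suitable for the pilot". The Discussion accepts that "it is not possible to blind local collaborators delivering the intervention".

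The Trial status section reads: "Recruitment commenced in November 2017 and is due to end in March 2019". Four is the only block size named anywhere in the article.

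**The concern.** The plan treats secrecy of the block size as a safeguard and then publishes the size in the sentence before. The people from whom it is to be kept are able to read the article, and they hold the other piece of information needed for prediction, namely past allocations at their own site. Because the list is stratified by site, the sequence that matters is the one seen locally.

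Emailing the allocation after pre-assessment delays the formal notice for the current couple. It does not prevent that couple's arm from being inferred from earlier ones.

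Three things are exposed:

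- **Selection.** Several entry criteria in Table 1 call for judgement, such as some ability to communicate, functional ability to engage, and a possible diagnosis. Whom to invite, and when, could be steered, knowingly or not.
- **Baseline scores.** The therapist who may have inferred the arm also administers the week 1 measures.
- **Main-trial planning.** Those scores are the pre-therapy values in the repeated measures ANOVA. The Data analysis section uses that analysis to choose a sensitive outcome and to calculate the sample size of the full trial. Both are conditions for proceeding under Criteria for success.

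**Working it through.** **Inputs.** Permuted blocks of four, 1:1, within site (Randomisation; abstract). 42 couples at seven sites (Sample size justification), so 42 / 7 = 6 per site. Equal accrual is an assumption. The observer is assumed to know the block size and every earlier allocation at the site. The 42 is a pragmatic recruitment estimate, so there is no power figure to reproduce.

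**Step 1: one block of four.** There are 6 equally likely orders of two A and two B.

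- 1st allocation: never certain; best guess right with probability 1/2.
- 2nd: never certain; guess the opposite arm, right with probability 2/3.
- 3rd: certain if the first two match (probability 1/3), otherwise even. Right with probability 1/3 + (2/3)(1/2) = 2/3.
- 4th: always certain.

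Certain per block: 1/3 + 1 = 1.33 of 4, or 33%. Correct guesses: 1/2 + 2/3 + 2/3 + 1 = 2.83 of 4, or 71%.

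**Step 2: six couples per site.** The 5th and 6th couples open a new block and add no certain allocations.

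- Certain: 1.33 / 6 = 22%. Over seven sites, 7 × 1.33 = 9.3 of 42.
- Correct guesses: 2.83 + 1/2 + 2/3 = 4.0 of 6, or 67%. Over seven sites, 28 of 42, against 21 by chance.

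**Step 3: other site sizes.** Certain share at three couples: (1/3) / 3 = 11%. At four: 33%. At eight: 2.67 / 8 = 33%.

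**Step 4: size known only from publication.** At a site of six, the allocations that can be certain are the 3rd and 4th. The number still to come depends on how many couples the site has already randomised:

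| Already randomised at each site | Certain allocations still to come, per site | Over seven sites |
|---|---|---|
| 0 to 2 | 1.33 | 9.3 |
| 3 | 1 | 7 |
| 4 or more | 0 | 0 |

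The article does not give its own publication date, so the whole range from 0 to 9.3 of 42 is open under these assumptions.

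**Step 5: sizes mixed at random between 4 and 6, six per site, set of sizes known.** Certainty now needs evidence that the first block is a six.

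- The first three alike: probability (1/2)(2/20) = 0.05. This makes the 4th certain.
- A 3:1 split after four: probability (1/2)(8/20) = 0.20. This makes the 5th and 6th certain.

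Certain: (0.05 × 1 + 0.20 × 2) / 6 = 0.45 / 6 = 7.5%. Exact enumeration gives 4.03 of 6 correct guesses, or 67.2%, essentially the same as with fixed fours.

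**Step 6: arm balance under the present plan.** With six per site, each site ends level with probability 2/3, or two apart in either direction with probability 1/6 each. Over seven sites, P(21:21) = 0.0585 + 0.1536 + 0.0480 + 0.0020 = 0.262, the terms being for 0, 1, 2 and 3 offsetting pairs of unbalanced sites.

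**The case against.** Fixed blocks of four within site are a common design, and the plan has partial safeguards. Someone other than the recruiters generates the list, allocation is released after pre-assessment, logs record ineligible people and decliners, and post-intervention assessors are blinded. These reduce other risks, but none stops an unblinded recruiter from inferring the next arm. The plural in "Block sizes will not be disclosed to local collaborators" might hint at varying sizes, but no size other than four is given.

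The objections to the size of the problem are stronger, and they stand:

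- The 22% and 67% assume the size is known from the first couple. Recruitment began in November 2017 and the article cites a registration dated 28/02/2018, so some recruitment time had passed before it appeared.
- They assume that one therapist sees the whole site sequence. The article says only that local collaborators are emailed allocations, and the Data management section's mention of a designated collaborator suggests that a site may have several.
- Six per site is an average, not a quota.

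A reader might also infer more than the documents support:

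- *That concealment is defeated.* Most allocations remain uncertain even in the worst case, and nothing shows that any therapist read the article or acted on it.
- *That the judgement on acceptability of randomisation would be distorted through decline rates.* Criteria for success bases that judgement on feedback forms.
- *That varying the block size cures guessing.* Step 5 shows that it does not if the set of sizes is known. Equally, fixed fours with the size unknown give no strictly certain allocations, so much of the protection comes from secrecy.

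**Conclusion.** The point holds as a weakness in concealment. The article states a rule of non-disclosure and breaks it in its own text, while the recruiters it is meant to bind are unblinded and still enrolling. The exposure applies to couples randomised after publication, at sites where a therapist both learns the size and knows the earlier allocations.

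At six couples per site the ceiling is 9.3 of 42 allocations certain (22%) and 28 of 42 guessed correctly (67%). The certain share is 11% at three per site and 33% at four or eight. The true figure is lower where therapists do not share allocations or where sites were well advanced at publication. The resulting bias in the group-by-time estimates cannot be quantified from the article. As this is a pilot with no efficacy threshold, the defect should be corrected but does not invalidate the study. Its main importance is for the outcome choice and sample size carried into the full trial.

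**What to change.** For couples not yet randomised, generate new lists for each site with randomly varying block sizes. Hold both the sizes and the set they are drawn from in a restricted document, outside any public or site paper, until the last couple is randomised. In the article, say only that allocation is by permuted blocks stratified by site, with details withheld during recruitment. Record that non-disclosure is an essential part of the measure, because varying sizes from a known set reduces certain foresight but hardly changes best-guess accuracy.

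The cost is seven short lists and slightly more chance imbalance, including up to two couples at a site where a block is abandoned part-way. Little is lost on balance: under the current scheme an exact 21:21 split has only 26% probability with six per site. The planned arms should be reported as about 21 couples each.
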